## Abstract

**Introduction:**

Immunomodulators such as thiopurines (azathioprine (AZA)/6-mercaptopurine (6MP)), methotrexate (MTX) and biologics such as adalimumab (ADA) are well established for maintenance of remission within paediatric Crohn’s disease (CD). It remains unclear, however, which maintenance medication should be used first line in specific patient groups.

**Aims:**

To compare the efficacy of maintenance therapies in newly diagnosed CD based on stratification into high and low-risk groups for severe CD evolution; MTX versus AZA/6MP in low-risk and MTX versus ADA in high-risk patients. Primary end point: sustained remission at 12 months (weighted paediatric CD activity index ≤12.5 and C reactive protein ≤1.5 fold upper limit) without relapse or ongoing requirement for exclusive enteral nutrition (EEN)/steroids 12 weeks after treatment initiation.

**Methods and analysis:**

REDUCE-RISK in CD is an international multicentre open-label prospective randomised controlled trial funded by EU within the Horizon2020 framework (grant number 668023). Eligible patients (aged 6–17 years, new-onset disease receiving steroids or EEN for induction of remission for luminal ± perianal CD are stratified into low and high-risk groups based on phenotype and response to induction therapy. Participants are randomised to one of two treatment arms within their risk group: low-risk patients to weekly subcutaneous MTX or daily oral AZA/6MP, and high-risk patients to weekly subcutaneous MTX or fortnightly ADA. Patients are followed up for 12 months at prespecified intervals. Electronic case report forms are completed prospectively. The study aims to recruit 312 participants (176 low risk; 136 high risk).

**Ethics and dissemination:**

ClinicalTrials.gov Identifier: (NCT02852694), authorisation and approval from local ethics committees have been obtained prior to recruitment. Individual informed consent will be obtained prior to participation in the study. Results will be published in a peer-reviewed journal with open access.

**Trial registration number:**

NCT02852694; Pre-results.

Strengths and limitations of this studyThis is the first international prospective randomised controlled trial comparing three different medications for maintenance of remission in newly diagnosed Crohn’s disease.This study may better define the most appropriate first-line immunomodulators based on a risk stratification protocol.Therapeutic efficacy will be supported by drug levels, pharmacogenomics and microbiome analysis as secondary outcomes.Inability to blind participants or treating physicians serves as a limitation to this study.Blinding of an alternative clinician to assess disease activity during study visits may prove practically difficult in smaller centres.

## Introduction

Crohn’s disease (CD), the most common form of inflammatory bowel disease (IBD) in children, is a chronic disorder with the potential to affect the whole gastrointestinal tract. The aim of CD treatment is to control active inflammation and achieve bowel healing. Chronic and uncontrolled CD results in poor outcomes for patients, including reduced quality of life, recurrent hospitalisation and potential need for surgical intervention.^1^ Treatments for CD are categorised into those which induce remission (such as steroids^1 2^ or exclusive enteral nutrition (EEN)^1 3^ and those which maintain remission. Immunomodulators are a mainstay of maintenance treatment in IBD, with the efficacy of thiopurines (eg, azathioprine (AZA) and 6-mercaptopurine (6MP))^4–6^ and methotrexate (MTX)^7–10^ well established. Antitumour necrosis factor (anti-TNF) therapies (infliximab^11 12^ and adalimumab (ADA)^13 14^ including their biosimilars were used in those patients refractory to ‘traditional’ induction or maintenance treatment. More recently in clinical practice, patients deemed as high risk have been treated with a biologic without the need for prior use of an immunomodulator.

Due to a lack of treatment strategy trials within the paediatric IBD (PIBD) population, however, it remains unclear which of the aforementioned maintenance therapies should be used first line in individual patients. Randomised controlled trials (RCTs) comparing the use of MTX with thiopurines for maintenance of remission failed to show a significant difference in efficacy between the two.^15–17^ A Cochrane review in adults with quiescent CD highlighted the lack of adequately powered trials necessary in order to determine the efficacy and safety of thiopurines compared with other maintenance therapies.^4 10^ The RISK study (observational, non-randomised study) demonstrated improved clinical and growth-based outcomes at 1 year with anti-TNF monotherapy in comparison with immunomodulators; however, further investigation into which specific patients are most likely to benefit from these therapies is still required.^18^ There is a clear disparity between North America and Europe in terms of which form of immunosuppression is used initially with both concerns about efficacy and safety lying behind these differences, thus, there is an urgent need for a head to head study in children to help objectively inform the primary choice of immunosuppression.

Stratifying patients by risk for complex or severe CD may allow pre-emptive direction of maintenance strategy and potentially an early reduction in disease burden with subsequent improvement in long-term outcomes. The adult IBD Ahead initiative highlighted young age at diagnosis as a risk factor for severity of CD evolution^19^; all patients diagnosed within paediatric services would therefore be considered ‘high risk’. Paediatric consensus guidelines suggest that paediatric CD patients at ‘high risk for poor outcome’ should receive early therapy optimisation to modify progression of their disease.^1^ The guidelines list specific features which may be considered predictive for poor outcome in paediatric CD (see table 1).^1^ Patients deemed at high risk for complex disease or poor outcome may benefit from a ‘top-down’ approach as the TISKids (an RCT from disease diagnosis) aims to investigate.^20^

**Table 1 T1:** Definition of high-risk patients based on ECCO/ESPGHAN consensus guidelines

Defining high-risk Crohn’s disease patients	
ECCO/ESPGHAN consensus guidelines	Modified study criteria
Severe perianal disease	Complex perianal fistulising disease phenotype
Extensive (pan-enteric) disease; deep colonic ulcers on endoscopy	Panenteric disease phenotype (defined as L3 with L4b as per Paris classification^25^ or L3 with deep ulcers in the duodenum, stomach or oesophagus not related to non-steroidal anti-inflammatory medications or *Helicobacter pylori*)
	Overall cumulative disease extent of >/=60 cm
Stricturing and penetrating disease at onset	B2, B3 or B2B3 disease behaviour^20^
Marked growth retardation ≥2.5 height Z scores	Severe growth impairment (height z-score ≤2 or crossing ≥2 centiles) likely related to Crohn’s disease
Persistent severe disease despite adequate induction therapy	Hypoalbuminaemia (<30 g/L), elevated CRP (at least two times upper limit of normal range), or wPCDAI >12.5 despite at least 3 weeks of optimised induction therapy with steroids or EEN
Severe osteoporosis	Not included

CRP, C reactive protein; ECCO, European Crohn’s and Colitis Organisation; EEN, exclusive enteral nutrition; ESPGHAN, European Society for Paediatric Gastroenterology, Hepatology and Nutrition; wPCDAI, weighted Paediatric Crohn’s Disease Activity Index.

Therefore, the PIBDnet consortium recognised the urgent need to investigate the efficacy and safety of immunomodulators and to investigate whether a top-down approach was superior to a traditional ‘step-up’ for paediatric patients deemed at high risk for rapidly complicated disease course. REDUCE-RISK in CD is an RCT which aims to compare the effectiveness of immunomodulators for maintenance of remission in newly diagnosed CD based on risk stratification specifically, the effectiveness of MTX versus AZA/6MP for maintenance of remission who are low risk for rapidly progressive disease and the effectiveness of MTX versus ADA in a high-risk group.

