## Methods and analysis

### Study design

We designed an international multicentre open-label prospective RCT with four treatment arms as shown in figure 1. Following screening and consent, eligible patients are stratified into low and high-risk groups based on phenotype and disease response to induction therapy (table 1). Patients are then randomised to one of two arms within their risk group, with low-risk patients receiving either weekly subcutaneous MTX or daily oral AZA/6MP and high-risk patients receiving either weekly subcutaneous MTX or fortnightly subcutaneous ADA.

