#### Inclusion visit and risk group allocation (week 5±3 weeks; visit 1)

In order to incorporate response to initial induction therapy within the risk stratification criteria, inclusion and risk group allocation is performed at week 5±3 weeks of induction therapy. Data from the screening visit are reviewed with ineligible patients excluded and patients are then stratified into the high or low risk group (table 1) based on the European Crohn’s and Colitis Organisation/European Society for Paediatric Gastroenterology, Hepatology and Nutrition consensus guidelines.^1^ Patients with perianal fistulising disease at diagnosis are auto allocated to the high-risk group regardless of other factors at inclusion visit. All other patients are allocated to the low-risk group. Patients with low thiopurine methyltransferase (TPMT) activity or homozygous mutations are excluded should they be categorised as low risk.

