### Randomisation and treatment allocation

Randomisation is undertaken following allocation to high or low-risk group at week 5±3 weeks. This process uses an integrated module within the electronic case report form (CRF) system. Within both the high and low-risk groups patients are 1:1 randomised to MTX vs ADA or AZA/6MP, respectively, in blocks of four stratified by EEN or steroid induction therapy. Code for randomisation is prepared and held by the central coordinating site and site coordinators are then informed of the results. Immunomodulator or biological therapy should be commenced within 2 weeks of randomisation as per the protocol outlined in table 2.

**Table 2 T2:** Medication protocol for low and high-risk patients following randomisation

	Therapy	Route	Dose	Notes
Low risk protocol	Methotrexate	SC	15 mg/m^2^ body surface area weekly (max dose 25 mg).	Ondansetron 4–8 mg orally 1-hour preinjection and folic acid 15 mg (5 mg in patients <20 kg) 3 days postinjection are recommended for all patients.

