#### Sample size considerations

Estimated remission rates are based on recent analysis from the RISK study,^18^ indicating an advantage of early anti-TNF introduction over immunomodulator therapy. For the low-risk group, it was hypothesised that 48% of children will be in remission at 12 months for the AZA/6MP arm versus 70% for the MTX arm. On the basis of this data with an alpha risk of 5% and a power of 80% a sample requirement of 88 patients per arm was calculated assuming a 10% lost to follow-up. For the high-risk group, it was hypothesised that 40% of children will be in remission at 12 months for the MTX arm versus 65% for the ADA arm. To detect this difference with an alpha risk of 5% and a power of 80%, a sample size of 68 participants is necessary, again assuming a 10% lost to follow-up. In total 312 participants will be included in the study (176 low-risk group; 136 high-risk group).

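### Risk allocation is allowed from week 2 of induction but the response criterion for high risk needs at least 3 weeks, so some children seen early are low risk by default

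*Protocol article*

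**What the plan says.** Three statements in the protocol article bear on this.

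- **Timing.** The section on the inclusion visit states that "inclusion and risk group allocation is performed at week 5±3 weeks of induction therapy". The section on randomisation repeats the window: "Randomisation is undertaken following allocation to high or low-risk group at week 5±3 weeks".
- **Response criterion.** In Table 1 (Introduction), the modified study criterion for persistent severe disease is albumin below 30 g/L, CRP at least twice the upper limit, or wPCDAI above 12.5, "despite at least 3 weeks of optimised induction therapy with steroids or EEN". The other study criteria are phenotypic and do not depend on time since induction: perianal disease, panenteric disease, extent of at least 60 cm, B2/B3 behaviour and growth impairment.
- **Default.** After describing the high-risk allocation, the inclusion visit section adds: "All other patients are allocated to the low-risk group".

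The purpose of the timing is stated in the same section: "In order to incorporate response to initial induction therapy within the risk stratification criteria". Study design says likewise that "eligible patients are stratified into low and high-risk groups based on phenotype and disease response to induction therapy (table 1").

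**The concern.** The lower end of the allocation window falls one week before the response criterion can first be met. The article gives no rule for a child seen in that week, such as deferral or reassessment. The default therefore treats a response that cannot yet be evaluated as if it were a good response.

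The risk group decides which randomised comparison a child enters: MTX against a thiopurine, or MTX against ADA. For the children concerned, the visit date can settle that question. Three things are at stake: what low risk means when results are reported, the remission rates behind the low-risk sample size, and the planned comparison of MTX between low- and high-risk patients. That last comparison is not randomised and depends directly on correct classification.

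**Working it through.** **1. Window against criterion.** Week 5 − 3 = week 2 and week 5 + 3 = week 8, so the window is 6 weeks long. The criterion needs at least 3 weeks, so it cannot be met from day 14 to day 20, which is 1 of the 6 weeks (17%). That is a share of the calendar window, not of patients.

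**2. The plan's own figure.** From Sample size considerations, "48% of children will be in remission at 12 months for the AZA/6MP arm versus 70% for the MTX arm", with 80% power; the two-sided 0.05 level is in Secondary analyses. The usual pooled-variance formula without continuity correction gives 78 per arm, and 78 / 0.90 = 86.7, so 87. The plan states 88, so its figure is reproduced to within one patient. With 10% lost, 88 × 0.90 = 79 evaluable per arm. The exact power of the Pearson test at 79 per arm, 70% v 48%, is 80.5%.

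**3. How many children could be misallocated.** Assumptions, none given in the documents:
- visits are spread evenly over the window, so 1/6 fall in weeks 2–3;
- the planned 176:136 split is the risk mix as observed;
- a share *r* of truly high-risk children qualify by response alone.

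The number of truly high-risk children is 136 / (1 − r/6). Of these, a fraction r/6 is misallocated, and the result is divided by 176.

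| r | Truly high risk | Misallocated | Share of low-risk group |
|---|---|---|---|
| 0.25 | 141.9 | 5.9 | 3.4% |
| 0.50 | 148.4 | 12.4 | 7.0% |
| 1.00 (ceiling) | 163.2 | 27.2 | 15.5% |

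**4. Effect on low-risk power.** Let *f* be the misallocated share. The MTX rate is (1 − f) × 0.70 + f × 0.40, where 0.40 is the plan's rate for high-risk MTX. The thiopurine rate is (1 − f) × 0.48 + f × t. The plan gives no value for t, so it is varied from 0.18 (which keeps a 22-point difference in these children) to 0.40 (no difference). Exact Pearson power at 79 per arm:

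| f | Difference at t = 0.18 | Power | Difference at t = 0.40 | Power |
|---|---|---|---|---|
| 0 | 22.0 points | 80.5% | 22.0 points | 80.5% |
| 3% | 22.0 | 80.0% | 21.3 | 77.7% |
| 7% | 22.0 | 79.6% | 20.5 | 73.7% |
| 15% | 22.0 | 79.0% | 18.7 | 65.2% |

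Example for f = 7%, t = 0.40: MTX 0.93 × 0.70 + 0.07 × 0.40 = 0.679; thiopurine 0.93 × 0.48 + 0.07 × 0.40 = 0.474; difference 20.5 points.

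**The case against.** The case for leaving this alone has several parts, and most of them limit the point rather than remove it.

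- **Few children are affected.** A child with any phenotypic criterion is high risk whenever seen; for perianal disease the article says so outright: "Patients with perianal fistulising disease at diagnosis are auto allocated to the high-risk group regardless of other factors at inclusion visit". This stands.
- **A child seen a week later need not be high risk.** A wPCDAI above 12.5 at week 2 may have settled by week 3, and such a child is rightly low risk. This stands. Only children still above a threshold at 3 weeks are misallocated.
- **The randomised comparisons are intact.** Patients are randomised 1:1 after allocation, within risk group, so both low-risk arms receive such children equally in expectation. This stands. A reader might infer that the low-risk treatment comparison is biased; the documents do not support that.
- **The treatment difference need not shrink.** That depends on a thiopurine rate in high-risk children which the article does not give. This stands.
- **The 3 weeks might qualify only wPCDAI.** Low albumin or raised CRP would then count earlier. The guideline entry in the same row, which speaks of persistence after adequate induction, tells against this reading, and the gap would remain for wPCDAI. Conversely, the criterion asks for optimised induction, which may begin after induction itself, so the gap could reach past week 3.
- **The full protocol may have a rule.** This is a condensed article and Figure 1 is not shown. That is possible, but the two timing rules and the default are all stated here and conflict as written.
- **The timing is called a pragmatic compromise in the Discussion.** It is, but the same paragraph gives as its reason that induction should have a chance to work before risk status is assigned.

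**Conclusion.** The inconsistency holds. Allocation is permitted one week before the response criterion can be met, and the default sends the affected children to the low-risk group, contrary to the stated aim of using response to induction. It concerns only children seen between weeks 2 and 3 who have no phenotypic criterion and remain active.

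The size is unknown. With evenly spread visits, the 176:136 mix, and a quarter to half of high-risk children qualifying by response alone, about 3–7% of the low-risk group would be misallocated, and at most about 15%. At 3–7%, power would be about 74–80% instead of 80.5%, given 40% remission on MTX and an assumed 18–40% on thiopurine in those children.

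A reader might go further and take the 17% of the window as the share misallocated, or conclude that visit date generally decides which comparison a child enters. Neither follows, because the phenotypic criteria apply at any visit. The main damage is to the meaning of the low-risk label and to the low- v high-risk MTX comparison; the loss of power is possible but not shown.

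**What to change.** - Reconcile Table 1 with the inclusion visit and randomisation sections, so that every child whose risk group depends on response can be evaluated against the criterion at allocation. Which passage changes is for the sponsor to decide. Children already high risk by phenotype need no response assessment, so the reconciled rule need not delay them.
- Add an eCRF check that enforces the reconciled rule.
- Flag children already allocated before 3 full weeks of induction.
- Add a sensitivity analysis, without those children, of the low-risk comparison and of the low- v high-risk MTX comparison.

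The cost is a minor amendment, an eCRF check and one extra analysis. The sample size need not change on this evidence. The count of flagged children will show whether the effect is material.

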## Methods and analysis

### Study design

We designed an international multicentre open-label prospective RCT with four treatment arms as shown in figure 1. Following screening and consent, eligible patients are stratified into low and high-risk groups based on phenotype and disease response to induction therapy (table 1). Patients are then randomised to one of two arms within their risk group, with low-risk patients receiving either weekly subcutaneous MTX or daily oral AZA/6MP and high-risk patients receiving either weekly subcutaneous MTX or fortnightly subcutaneous ADA.

**Figure 1 F1:**
[figure not shown]
Study design of the REDUCE-RISK in CD trial. M2=month 2, V2=visit 2. EN, enteral nutrition; PCDAI, Paediatric Crohn’s Disease Activity Index; PGA, physician global assessment; wPCDAI, weighted PCDAI.

### Study end points

Patients are followed up for 12 months postrandomisation. The primary end point of the study is sustained steroid or EEN-free remission at 12 months, defined as weighted Paediatric Crohn’s Disease Activity Index (wPCDAI) ≤12.5 and C reactive protein (CRP) ≤1.5 fold upper limit without a relapse or need for EEN/steroids since week 12.

Secondary end points include comparison of time to first relapse, remission at 12 weeks, growth, adverse events, health-related quality of life and patient-reported outcomes between the two treatment arms within each risk group but also between low and high risk MTX treated patients (a full list of secondary endpoints can be found in box 1). The TUMMY CD (patient-related outcome measure) was originally included as a secondary end point but has been withdrawn as the original timetable of development and validation of the score has not been met so it was not ready in time to be included. The study also aimed to evaluate clinical predictors for response, including genomic and serological markers and results of drug monitoring (MTX and ADA concentrations) metabolites (6-thioguanine (6-TG) and 6-methylmercaptopurine (6-MMP) in AZA/6MP) and antidrug antibodies (ADA) in relation to adherence, toxicity and response. The ancillary study additionally aimed to evaluate the efficacy of ADA in patients treated from inclusion (top-down) versus patients switched to ADA due to immunomodulator failure (step-up). Further outcome measures are detailed in box 1.

Box 1Study endpointsPrimary endpointSustained steroid/exclusive enteral nutrition (EEN)-free remission at month 12, where sustained remission is defined as weighted Paediatric Crohn’s Disease Activity Index (wPCDAI) ≤12.5 and C reactive protein (CRP) ≤1.5 times the upper limit without a relapse or need for EEN/steroids since week 12.Secondary endpointsComparing the following within (1) the two treatment arms per risk group; (2) methotrexate treatment between high and low-risk groups and (3) tOP-down adalimumab (high-risk group) versus step-pp adalimumab (ancillary study):Rate of clinical remission at month 12 (physician global assessment, wPCDAI, PCDAI).Relapse free remission with normal CRP at month 12.Relapse-free remission with normal CRP and faecal calprotectin <300 at month 12.Remission at week 12 (measured by wPCDAI≤12.5 and normal CRP and being off steroids/EEN).Time to first relapse after week 12.Predictive value of faecal calprotectin values at visits 1, 2, 4 and 6 (respectively at month 0, 2, 6 and 12).Drop-out rates.Adverse drug event rate including pharmacogenomics for toxicity and response to therapy.Height velocity and z-score at baseline and 52 weeks.Quality of life as measured by the IMPACT 3 questionnaire completed at each study visit.Health economic evaluation at all visits (forms EQ-5D-Y proxy 1, EQ-5D-Y and EQ-5D-5L, Productivity and Activity Impairment Questionnaire (WPAI):Crohn’s disease Caregiver, School Attendance start of the research and follow-up visits).

